### **3.4 Screening & Enrollment Procedures**

Each site will maintain a screening log showing all patients admitted with PROM. The log will record a disposition for each patient, from the following checkbox choices:

1. not eligible for trial (one or more inclusion criteria not met, list criteria not met)
2. eligible but not approached for enrollment
3. approached but patient declined to consent
4. informed consent obtained but not randomized
5. randomized

With the permission of the patient's attending physician, eligible patients will be approached by study personnel, will receive an explanation of the study procedures, risks, benefits & alternatives, and will be asked to voluntarily consent to the study. If consent is obtained and appropriately signed, dated, and witnessed, an order will be recorded in the medical record directing the inpatient pharmacy to assign a randomization code to the patient and to dispense a weekly dose of study medication (either 17P or placebo.) The enrolled participant will be entered onto an enrollment log and capture the enrollment information.

### **3.5 Group Assignment, Study Medications**

Each patient will be randomly assigned to one of two treatment arms, 17P or placebo.

a. Progesterone (17P) group. Patients in the 17P group will be given 17P, 250 mg IM weekly in 1 ml of oil vehicle.

b. Placebo group. Patients in the placebo group will be given a weekly IM injection of 1 ml of oil vehicle.

Patients, investigators, and study personnel will be blinded as to group assignment. A computer randomization program will be used to generate a randomization code book which will be kept at the pharmacy at each study site hospital. The pharmacy will use the code-book to determine which medication to dispense (17P or placebo) to the patient. The code will not be broken or revealed until all patients have completed the study & their data submitted, unless the data safety/monitoring committee concludes that breaking the code is necessary to evaluate an adverse event.

To ensure balanced group assignments at each study site, randomization will be stratified in 3-week gestational age strata (23w0d-25w6d, 26w0d-28w6d, 29w0d-31w6d).

The assigned medication will be administered by a registered nurse. The administration will be recorded in the inpatient medical record, for example, “Study medication, progesterone or placebo, 1 ml, IM injection in right ventral gluteus” or similar notation as required per hospital policy at each site. The research personnel will also document the medication administration on the participant’s case report form..

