### **3.6 Management Common to All Patients, Regardless of Group Assignment**

a. Hospital admission until delivery. All enrolled patients will be admitted for inpatient management until delivery. An exception will be made if the membranes reseal, as discussed at the end of this section.

Antenatal corticosteroids. All patients will be given a single course of antenatal corticosteroids with an intention to accelerate fetal lung maturation. A “course” of corticosteroids is defined as either:

(a) two doses of betamethasone, 12 mg IM, given at 24 hr intervals OR

(b) four doses of dexamethasone, 6 mg IM, given at 12 hr intervals

Betamethasone is preferred. Dexamethasone may be used if betamethasone is unavailable or if the patient has already been started on dexamethasone. If the patient received a complete course of corticosteroids at any time after 22w0d and before enrollment, no further corticosteroids will be given. That is, she will not be given so-called “rescue steroids”. If the patient received a partial course within the 2 days prior to enrollment, the remaining dose(s) of the same medication will be given. If the patient received a partial course more than 2 days prior to enrollment, a complete course will be given upon enrollment.

Prophylactic antibiotics. All patients will receive a course of antibiotic prophylaxis. Each study site has a slightly different standard regimen for prophylaxis after PROM, but all use broad-spectrum antibiotics for 5-7 days in regimens similar to that of Mercer et al. (1997). The prophylactic antibiotics used, dosage, and route of administration will be recorded in the case report form for each participant.

Antibiotics for Labor & Delivery. Antibiotic therapy is frequently used during labor or frequently used preoperatively for cesarean delivery in patients with PROM. The choice of antibiotic regimen for these indications is left to the patient’s attending physician. The dosage

and route of peripartum antibiotics used, if any, will be recorded in the case report form for each participant.

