Vaginal amniotic fluid specimen for FLM at 32 wks, if possible. If the patient reaches a gestational age of 32w0d during expectant management & if she is still leaking amniotic fluid, an attempt will be made to obtain a sample of fluid leaked from the vagina for assessment of fetal lung maturity. A fluid sample collected by amniocentesis may be used in lieu of a vaginally collected sample if there is an indication for amniocentesis at 32w0d or more. Each study site will use its customary test for fetal lung maturity. Tests in use at our study sites include TDX-FLM2™, lecithin/sphingomyelin ratio, phosphatidylglycerol, and lamellar body counts. If fetal lung maturity is documented, delivery will be initiated. If it is not possible to obtain a fluid specimen or if the fluid does not indicate lung maturity, then expectant management will be continued until 34w0d of gestation & delivery initiated at that time. All study site investigators agree that continued expectant management is not reasonable after 34 weeks of gestation. Beyond 34 wks, the risks of premature delivery are small compared to the risks of attempted expectant management (IAI, cord accident, and abruption, any of which can be lethal.)

Route of Delivery. Vaginal delivery will ordinarily be attempted unless there is a standard obstetric indication for cesarean delivery, including malpresentation, abnormalities of the fetal

heart rate tracing, or a history of prior cesarean delivery. The route of delivery will be at the discretion of the attending physician in consultation with the patient.

Membrane resealing. To diagnose resealing, the following 3 criteria must all be present (a, b, and at least one part of c).

- a. the patient reports cessation of fluid leakage for at least 72 hrs, and then no fluid leakage occurs after a 1-day trial of light ambulation
- b. ultrasound exam shows normal amniotic fluid volume (four-quadrant fluid index of 8 cm or more)
- c. at least ONE of the following confirmatory tests is documented:
  - i. Amnisure (TM) of cervicovaginal secretions is negative
  - ii. Fetal Fibronectin test of cervicovaginal secretions is negative
  - iii. Speculum examination shows no pooling of fluid and fern and nitrazine tests are both negative.
  - iv. Indigo carmine dye instilled in the amniotic sac via amniocentesis does not leak vaginally within 24 hrs

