### **3.7 Study Outcomes**

1. Primary outcome: Pregnancy continues until 34w0d of gestation or documentation of lung maturity at 32w0d to 33w6d.

2. Secondary outcomes:

a. duration of latency period (time from randomization to delivery)

b. composite neonatal morbidity, defined as one or more of the following, using the definitions of Mercer et al. (1997):

i. stillbirth

ii. neonatal death

iii. infant death before hospital discharge

iv. respiratory distress syndrome (RDS)

v. intracranial hemorrhage (ICH), grade 3 or 4

vi. necrotizing enterocolitis (NEC), stage 2 or 3

vii. documented neonatal sepsis within 72 hr of birth

viii. periventricular leukomalacia (PVL): characteristic lesions in the subcortical white matter seen on cerebral imaging studies within 96 hrs of birth (not included in the definitions of Mercer et al. (1997))

3. Tertiary outcomes

a. gestational age at delivery

b. route of delivery

c. neonatal length of stay

d. birth weight

e. Apgar scores

f. Amnionitis

g. Postpartum endometritis

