### **3.9 Data Analysis**

Primary Outcome. The primary outcome measure is the proportion of women who continue the pregnancy to a favorable gestational age (34w0d or documented fetal lung maturity at 32w0d to 33w6d). The null and alternative hypotheses are as follows:

$$H_0: p_1 = p_2 \text{ and } H_1: p_1 \neq p_2$$

where  $p_1$ =the proportion of women who continue the pregnancy to a favorable gestational age in the progesterone group and  $p_2$ =the proportion of women who continue the pregnancy to a favorable gestational age in the placebo group

To test the null hypothesis, a Cochran-Mantel-Haenszel test will be used, stratified by gestational age group at randomization. The final alpha level will be based on the O'Brien-Fleming spending function and depends on the number and timing of interim analyses. If, as planned, only one interim analysis occurs at 50% of participants randomized, the final alpha level will be

0.049. The primary outcome measure will be analyzed in the intent-to-treat population (i.e. all randomized participants).

Secondary Outcomes. The duration of latency will be determined as the time from randomization until delivery. A staggered entry Kaplan-Meier analysis (which adjusts for gestational age at randomization) will be completed with participants with missing outcome data censored on the date last known pregnant. Significant differences between the progesterone and placebo group will be determined using the log-rank test.

The percentage of participants with at least one of the neonatal morbidity measures (composite neonatal morbidity) will be tested for significant differences between the treatment groups using a Cochran-Mantel-Haenszel test stratified by gestational group at randomization. The percentage of participants with each of the component morbidities (e.g. RDS, NEC, IVH, etc.) will be similarly compared.

All secondary outcome measures will be tested for statistical significance using an alpha level of 0.05. Latency and composite neonatal morbidity will be analyzed in the intent-to-treat population. With the exception of stillbirth (analyzed in the intent-to-treat population), the component morbidities will be analyzed in all participants with a live birth.

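### Section 3.5 promises balance at each site but names only gestational age; if the pharmacy lists are by site, the CMH tests in 3.9 omit a randomisation factor at a small cost in power

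*Protocol*

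**What the plan says.** Protocol section 3.5 gives the aim and the method in one sentence: "To ensure balanced group assignments at each study site, randomization will be stratified in 3-week gestational age strata". The three bands are 23w0d-25w6d, 26w0d-28w6d and 29w0d-31w6d. Site is not named as a factor and blocking is not mentioned. The same section describes a "randomization code book which will be kept at the pharmacy at each study site hospital", and section 3.4 has the inpatient pharmacy assign the code.

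For the primary outcome, section 3.9 says "a Cochran-Mantel-Haenszel test will be used, stratified by gestational age group at randomization". Composite neonatal morbidity is tested with the same strata. Site appears in neither test.

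The primary outcome (section 3.7) is "Pregnancy continues until 34w0d of gestation or documentation of lung maturity at 32w0d to 33w6d". Section 3.6 lets practice vary between sites: "Each study site will use its customary test for fetal lung maturity", and "Each study site has a slightly different standard regimen for prophylaxis after PROM". It also says "If fetal lung maturity is documented, delivery will be initiated". On blinding, section 3.5 says "Patients, investigators, and study personnel will be blinded as to group assignment".

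**The concern.** The stated method does not by itself achieve the stated aim. Stratifying on gestational age equalises the arms within each band. It equalises them within each hospital only if the lists are also separate by hospital and restricted, for example by blocks.

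If the lists are separate by site, as the pharmacy arrangement implies, a second mismatch follows. The trial then randomises within site and gestational-age band but analyses within gestational-age band only. Section 3.6 gives reasons why site could be prognostic. A documented mature result at 32w0d to 33w6d is one of two routes to success, and each site uses its own test for it. When a prognostic factor is balanced by design and left out of the test, the test overstates its own variance. It stays valid but becomes conservative, and some power is lost.

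**Working it through.** **1. The plan's own figures.** Inputs from section 3.9: 30% against 50%, two-sided 5%, 80% power, one interim look.

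- Per group, n = [1.96·√(2·0.4·0.6) + 0.8416·√(0.3·0.7 + 0.5·0.5)]² / 0.2² = (1.358 + 0.571)² / 0.04 ≈ 93.
- With a continuity correction this is 103, and 104 at the final alpha of 0.049. The protocol has 105.
- 105 / 0.95 = 110.5, so 111 per group and 222 in all.
- The Lan-DeMets O'Brien-Fleming function at half information gives 0.00305 and 0.0490, matching 0.0031 and 0.049.

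These figures are not in question.

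**2. What each reading of section 3.5 does to balance.** Simulation of 222 women. The following are assumptions, not protocol figures: 5, 10 or 15 sites of unequal size; gestational-age mix 25/35/40%; blocks of 4 where blocked. The measure is the largest difference between arms at any one site, over the three site numbers.

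| Allocation | Mean | 95th percentile |
|---|---|---|
| Unblocked | 8.4 to 10.8 | 13 to 19 |
| Blocked by gestational age, shared across sites | 7.9 to 8.9 | 12 to 16 |
| Blocked by site and gestational age | 2.4 to 3.2 | 4 |

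Only the last row delivers what section 3.5 promises.

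**3. Could site matter?** Section 2.2 gives a latency half-life of about one week. Let m be the share of women undelivered at 32w0d in whom the site then documents maturity. Their chance of success is m + (1 − m)·0.5². With m = 0 this is 25%; with m = 0.5 (illustrative) it is 62.5%.

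**4. Cost of leaving site out when lists are blocked by site.** Further assumptions: placebo success 15/25/44% by band (0.25·15 + 0.35·25 + 0.40·44 ≈ 30%); treatment log-odds 0.93, which takes the average to about 50% when sites do not differ; final critical value 1.969; 4,000 runs per cell (simulation error about ±0.007 on type I error). SD is the between-site SD of log-odds. Planned means CMH by gestational age; full means CMH by gestational age × site, unpooled. Differences are taken before rounding.

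| Sites | SD | Type I planned / full | Power planned / full (%) | Difference (points) |
|---|---|---|---|---|
| 5 | 0 | 0.048 / 0.046 | 89.8 / 89.5 | −0.3 |
| 5 | 0.5 | 0.043 / 0.048 | 87.0 / 87.7 | +0.7 |
| 5 | 1.0 | 0.035 / 0.046 | 81.4 / 84.9 | +3.5 |
| 10 | 0 | 0.050 / 0.051 | 88.8 / 88.1 | −0.7 |
| 10 | 0.5 | 0.041 / 0.047 | 86.6 / 86.9 | +0.3 |
| 10 | 1.0 | 0.036 / 0.051 | 81.1 / 84.2 | +3.1 |
| 15 | 0 | 0.050 / 0.051 | 90.3 / 88.9 | −1.4 |
| 15 | 0.5 | 0.046 / 0.046 | 87.5 / 86.9 | −0.6 |
| 15 | 1.0 | 0.033 / 0.052 | 79.0 / 81.9 | +2.9 |

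The cost of omitting site is the difference within a row. The fall in power down the SD column is not that cost: with the log-odds effect held fixed, wider site spread also shrinks the average risk difference.

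**5. With small sites pooled.** A further simulation over 5 to 15 sites, with site-blocked lists, put the planned test's type I error at about 0.036 to 0.044 at SD 1.0. Adding site with small sites pooled gained 2 to 4 points of power at SD 1.0 and cost at most about 0.4 points when sites barely differed.

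**6. If lists are not blocked by site.** Type I error of the planned test was 0.042 to 0.057, within simulation error of 0.049. At 15 sites and SD 0.5, the full site × gestational-age CMH then lost about 5 to 6 points of power (about 87% to 81-82%).

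**The case against.** The best defence is that section 3.5 already means site-specific lists. The code book sits at each hospital's pharmacy, the pharmacy assigns the code, and no central allocation is described. Block structure commonly belongs in a randomisation plan. This largely stands. A reader might infer from section 3.5 that balance by site is impossible under this design; the document does not support that. The gap is that the factor and the restriction are implied rather than stated.

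A reader might also infer that site differences in lung-maturity testing bias the primary comparison. They do not. Allocation is random and blinded, so site practice is independent of arm in expectation, and chance imbalance is covered by alpha. No simulated scenario showed type I inflation beyond simulation error.

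The assumed SD of 1.0 is also generous. Around a 30% rate it puts sites at ±1 SD at about 14% and 54%. The lung-maturity route alone supports less. If a proportion q of women reach 32w0d, site success runs from 0.25q to 0.625q. For q from 0.1 to 0.8, half the sites at each extreme gives an SD of 0.48 to 0.69, and an even spread about 0.27 to 0.39. Sites are also less free than they may look: a sample is to be attempted in every woman still leaking at 32w0d, and all antibiotic regimens are broad-spectrum for 5-7 days. So the likely power loss is at the low end.

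Finally, adding site can do harm if done crudely. Fifteen sites by three bands makes 45 strata for 222 women, about five each. Nor would it make the lung-maturity tests comparable. Both points stand and shape the fix.

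**Conclusion.** The point holds as a gap in section 3.5 and a mismatch between sections 3.5 and 3.9. As written, gestational-age strata secure balance at each site only if each pharmacy's list is separate and blocked within band, which is implied and not stated. If so, the CMH tests omit a randomisation factor. The consequence is a valid but conservative test, losing about 2 to 4 points of power at a between-site SD of 1.0 and essentially none at 0.5 or below. These sizes rest on an assumed 5 to 15 sites, blocks of 4, and assumed gestational-age mix and stratum rates. Even at SD 1.0 the planned test kept about 79% to 81% power, close to the 80% target. The reason to change is that the analysis should follow the randomisation and that doing so costs almost nothing; the trial's validity is not at risk.

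**What to change.** - **Section 3.5:** state that randomisation is stratified by site and by the three gestational-age bands, with a separate blocked list for each site. Block sizes can stay in a restricted randomisation document.
- **Section 3.9:** stratify the primary and composite-morbidity CMH tests by gestational-age band and site, with small sites pooled by a rule fixed before unblinding. Pooling small sites that use the same lung-maturity test is one natural rule.
- Do not use the full unpooled site × gestational-age strata if sites prove many and small. At 15 sites with no site differences, that cost about 1 to 3 points of power across the simulations with site-blocked lists, and more where lists were not blocked by site.

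The cost is one sentence in each section and, with pooling, a negligible loss of information if sites do not differ.

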### **3.6 Management Common to All Patients, Regardless of Group Assignment**

a. Hospital admission until delivery. All enrolled patients will be admitted for inpatient management until delivery. An exception will be made if the membranes reseal, as discussed at the end of this section.

Antenatal corticosteroids. All patients will be given a single course of antenatal corticosteroids with an intention to accelerate fetal lung maturation. A “course” of corticosteroids is defined as either:

(a) two doses of betamethasone, 12 mg IM, given at 24 hr intervals OR

(b) four doses of dexamethasone, 6 mg IM, given at 12 hr intervals

Betamethasone is preferred. Dexamethasone may be used if betamethasone is unavailable or if the patient has already been started on dexamethasone. If the patient received a complete course of corticosteroids at any time after 22w0d and before enrollment, no further corticosteroids will be given. That is, she will not be given so-called “rescue steroids”. If the patient received a partial course within the 2 days prior to enrollment, the remaining dose(s) of the same medication will be given. If the patient received a partial course more than 2 days prior to enrollment, a complete course will be given upon enrollment.

Prophylactic antibiotics. All patients will receive a course of antibiotic prophylaxis. Each study site has a slightly different standard regimen for prophylaxis after PROM, but all use broad-spectrum antibiotics for 5-7 days in regimens similar to that of Mercer et al. (1997). The prophylactic antibiotics used, dosage, and route of administration will be recorded in the case report form for each participant.

Antibiotics for Labor & Delivery. Antibiotic therapy is frequently used during labor or frequently used preoperatively for cesarean delivery in patients with PROM. The choice of antibiotic regimen for these indications is left to the patient’s attending physician. The dosage

and route of peripartum antibiotics used, if any, will be recorded in the case report form for each participant.

Tocolytic therapy. Medications intended to suppress contractions may be used at the discretion of the attending physician during the first 48 hrs after administration of the first dose of corticosteroids. Thereafter, such medications will not be used. These medications include magnesium sulfate, terbutaline, nifedipine (and other calcium channel blockers), & indomethacin (and other cyclooxygenase inhibitors or nonsteroidal anti-inflammatory drugs such as ibuprofen, celecoxib, or sulindac.)

Amniocentesis to rule-out intraamniotic infection (IA). We encourage investigators to perform amniocentesis & to evaluate the preliminary (“stat”) results before randomizing patients into this study. After randomization, amniocentesis may become clinically indicated to evaluate suspected IAI in some cases. If performed, fluid will be sent for gram stain, glucose, WBC, and culture, with interpretation as per the discussion above, and for fetal lung maturity studies if performed between 32w0d and 33w6d.

Fetal heart rate monitoring. At least one hour of fetal monitoring every day will be performed. Additional monitoring will be allowed per the discretion of the patient’s attending physician.

Avoidance of Digital Examination of the Cervix. Because insertion of a gloved finger into the cervix might introduce vaginal bacteria into the uterus, thereby increasing the risk of intraamniotic infection, digital examination of the cervix is generally discouraged while

attempting expectant management of PROM. Most obstetricians have been trained to examine the cervix by visual inspection via speculum examination. This is the preferred method for patients in this study. The number & timing of digital examinations & speculum examinations performed before the onset of active labor will be tabulated in the case report form for each participant.

Vaginal amniotic fluid specimen for FLM at 32 wks, if possible. If the patient reaches a gestational age of 32w0d during expectant management & if she is still leaking amniotic fluid, an attempt will be made to obtain a sample of fluid leaked from the vagina for assessment of fetal lung maturity. A fluid sample collected by amniocentesis may be used in lieu of a vaginally collected sample if there is an indication for amniocentesis at 32w0d or more. Each study site will use its customary test for fetal lung maturity. Tests in use at our study sites include TDX-FLM2™, lecithin/sphingomyelin ratio, phosphatidylglycerol, and lamellar body counts. If fetal lung maturity is documented, delivery will be initiated. If it is not possible to obtain a fluid specimen or if the fluid does not indicate lung maturity, then expectant management will be continued until 34w0d of gestation & delivery initiated at that time. All study site investigators agree that continued expectant management is not reasonable after 34 weeks of gestation. Beyond 34 wks, the risks of premature delivery are small compared to the risks of attempted expectant management (IAI, cord accident, and abruption, any of which can be lethal.)

Route of Delivery. Vaginal delivery will ordinarily be attempted unless there is a standard obstetric indication for cesarean delivery, including malpresentation, abnormalities of the fetal

heart rate tracing, or a history of prior cesarean delivery. The route of delivery will be at the discretion of the attending physician in consultation with the patient.

Membrane resealing. To diagnose resealing, the following 3 criteria must all be present (a, b, and at least one part of c).

- a. the patient reports cessation of fluid leakage for at least 72 hrs, and then no fluid leakage occurs after a 1-day trial of light ambulation
- b. ultrasound exam shows normal amniotic fluid volume (four-quadrant fluid index of 8 cm or more)
- c. at least ONE of the following confirmatory tests is documented:
  - i. Amnisure (TM) of cervicovaginal secretions is negative
  - ii. Fetal Fibronectin test of cervicovaginal secretions is negative
  - iii. Speculum examination shows no pooling of fluid and fern and nitrazine tests are both negative.
  - iv. Indigo carmine dye instilled in the amniotic sac via amniocentesis does not leak vaginally within 24 hrs

If membrane resealing is documented, the patient will be discharged from the hospital for self-care at home. The study medications (progesterone vs placebo) and prophylactic antibiotics will be discontinued upon discharge from the hospital. An attempt will be made to capture delivery & neonatal outcome data, even if delivery occurs at another hospital. For analysis under the “intent-to-treat” principle, the patient will be included with her originally-assigned group (progesterone or placebo).

